# Testing the therapeutic effects of transcranial direct current stimulation (tDCS) in semantic dementia: a double blind, sham controlled, randomized clinical trial

**DOI:** 10.1186/s13063-019-3613-z

**Published:** 2019-11-20

**Keywords:** Non-invasive brain stimulation, Transcranial direct current stimulation, Semantic dementia, Primary progressive aphasia, Language impairments, Neurodegenerative diseases, Neurology

## Abstract

**Background:**

Semantic dementia is a neurodegenerative disease that primarily affects the left anterior temporal lobe, resulting in a gradual loss of conceptual knowledge. There is currently no validated treatment. Transcranial stimulation has provided evidence for long-lasting language effects presumably linked to stimulation-induced neuroplasticity in post-stroke aphasia. However, studies evaluating its effects in neurodegenerative diseases such as semantic dementia are still rare and evidence from double-blind, prospective, therapeutic trials is required.

**Objective:**

The primary objective of the present clinical trial (STIM-SD) is to evaluate the therapeutic efficacy of a multiday transcranial direct current stimulation (tDCS) regime on language impairment in patients with semantic dementia. The study also explores the time course of potential tDCS-driven improvements and uses imaging biomarkers that could reflect stimulation-induced neuroplasticity.

**Methods:**

This is a double-blind, sham-controlled, randomized study using transcranial Direct Current Stimulation (tDCS) applied daily for 10 days, and language/semantic and imaging assessments at four time points: baseline, 3 days, 2 weeks and 4 months after 10 stimulation sessions. Language/semantic assessments will be carried out at these same 4 time points. Fluorodeoxyglucose positron emission tomography (FDG-PET), resting-state functional magnetic resonance imaging (rs-fMRI), T1-weighted images and white matter diffusion tensor imaging (DTI) will be applied at baseline and at the 2-week time point. According to the principle of inter-hemispheric inhibition between left (language-related) and right homotopic regions we will use two stimulation modalities - left-anodal and right-cathodal tDCS over the anterior temporal lobes. Accordingly, the patient population (*n* = 60) will be subdivided into three subgroups: left-anodal tDCS (*n* = 20), right-cathodal tDCS (*n* = 20) and sham tDCS (*n* = 20). The stimulation will be sustained for 20 min at an intensity of 1.59 mA. It will be delivered through 25cm^2^-round stimulation electrodes (current density of 0.06 mA/cm^2^) placed over the left and right anterior temporal lobes for anodal and cathodal stimulation, respectively. A group of healthy participants (*n* = 20) matched by age, gender and education will also be recruited and tested to provide normative values for the language/semantic tasks and imaging measures.

**Discussion:**

The aim of this study is to assess the efficacy of tDCS for language/semantic disorders in semantic dementia. A potential treatment would be easily applicable, inexpensive, and renewable when therapeutic effects disappear due to disease progression.

**Trial registration:**

ClinicalTrials.gov NCT03481933. Registered on March 2018.

**Electronic supplementary material:**

The online version of this article (10.1186/s13063-019-3613-z) contains supplementary material, which is available to authorized users.

## Introduction

Semantic dementia (SD), also referred to as the semantic variant of primary progressive aphasia (sv-PPA) [1], is part of the spectrum of frontotemporal lobar degeneration and constitutes one of the major clinical variants of this disorder [2]. The onset age of SD is frequently before 65 years [3] and it severely affects the ability to communicate, which generates a major impact on the family and socio-professional life of patients.

SD is characterized by a gradual and severe loss of conceptual knowledge, resulting in anomia, impaired word comprehension and speech that is fluent but empty of content [2], leaving grammar and speech articulation preserved [4]. Although the most prominent deficits concern word meaning [1, 4], SD might eventually cause deterioration of knowledge for all kinds of semantic concepts [5, 6] impacting on face recognition [7], object feature attribution [8], sound-picture matching [9] and object-use [10]. The damage to multi-modal semantic representations, besides the verbal domain, gave birth to the concept of semantic dementia [11]. It therefore appears that sv-PPA is a purely linguistic variant of SD [12] and/or that SD results from the evolving disease course of sv-PPA [13, 14].

At the anatomical level SD affects the anterior temporal lobe (ATL) of both hemispheres, predominantly in left lateralized regions [1, 4]. Correlation has been identified between gray matter loss in the ATL and different semantic tasks like picture naming [15, 16] and word-picture association [17]. It is associated with disruptions of functional connectivity between a broad range of brain regions across the temporal, frontal, parietal and occipital lobes, including visual and auditory association cortices [18]. Alterations of structural connectivity such as a white matter volume reduction in the left temporal lobe, the periventricular white matter and the corpus callosum [19], and damage to white matter tracts such as the inferior longitudinal fasciculus (ILF) and the uncinate fasciculus (UF) have also been found in SD [20]. Signs of cortical hypometabolism, which are a useful neuroimaging hallmark for diagnosis have mainly been found in the ATL cortices, sometimes extending to the subgenual region and the right anterior cingulate cortex [21].

There is currently no validated treatment for SD given that speech therapy protocols have not been validated and pharmacological trials did not demonstrate significant effects [22–24]. In this context, new approaches based on the use of non-invasive brain stimulation and neuro-modulation [25] might represent a promising therapeutic strategy. Two of the most common technologies for non-invasive brain stimulation are repetitive transcranial magnetic stimulation (TMS) and transcranial direct current stimulation (tDCS) [26]. Repetitive TMS involves the application of a series of magnetic pulses through a stimulating coil placed in contact with an area of the scalp. In a frequency-dependent and pattern-dependent manner, this stimulation technology induces an intracranial electric current that subsequently modulates (inhibits or facilitates) neuronal activity [26]. Repetitive TMS is characterized by its excellent spatial and temporal resolution and ability to make neurons discharge, features that come at the cost of low portability, high financial cost and epileptic risk. The effects of tDCS are based on a weak electric current (1–2 mA) conveyed between two electrodes (an active and a return) placed on separate locations of the scalp, with the ability to generate a polarization gradient across a large cortical area between electrodes, hence modulating cortical excitability within its boundaries [27]. Two modalities of tDCS are commonly used: Anodal and Cathodal stimulation. Anodal stimulation (in which the anode is placed on the targeted region) shifts the membrane resting potential of local neurons bringing it closer to their firing threshold (i.e. making it more positive hence depolarizing local cells). This modality increases regional excitability and facilitates the activation of neurons hence the production of action potentials in response to physiological inputs (excitatory effects). Cathodal stimulation (in which the cathode is placed on the targeted region), shifts the resting membrane potential of nearby neurons away from their firing threshold (i.e., making it more negative, hence hyperpolarizing local cells). Consequently, this modality decreases regional excitability hindering the likelihood of such neurons to generate an action potential in response to a physiological input (inhibitory effects).

For several years a growing number of studies have explored the effects of non-invasive brain stimulation in patients with aphasia following left hemisphere strokes. These studies rely on the assumption that weak electrical currents can interact with neural networks subtending language and promote neural plasticity, allowing short-term modulations, and eventually clinical recovery. Within these language-related networks, left and right homotopic regions are connected via transcallosal connections [28, 29] which, according to the principle of inter-hemispheric inhibition, tend to convey mutual net inhibitory influences [30]. The use of non-invasive brain stimulation in left hemisphere stroke aphasia relies on three potential mechanisms or combinations thereof [31, 32]: (1) the use of left-excitatory (anodal tDCS or high-frequency TMS) stimulation on left hemisphere language systems to reactivate language processes implemented by peri-lesional regions; (2) the delivery of right-inhibitory (cathodal tDCS or low-frequency TMS) stimulation to reduce the inhibition that right hemisphere systems exert on the left dominant language network and (3) the delivery of right-excitatory stimulation to activate potential language contributions of right hemisphere networks. The most promising clinical outcomes on language disabilities have been achieved from studies adopting the first two approaches using either TMS (e.g., see [33–36]) or tDCS (e.g., see [37–39]). Beneficial effects have been shown either transiently with single-session applications, or as longer-lasting impacts (> 6 months) following periodical stimulation sessions across several days, probably related to stimulation-induced neuroplasticity [34, 40].

Non-invasive brain stimulation has also been used with relative efficacy in Alzheimer’s disease by targeting the left and/or right dorsolateral prefrontal cortex [41, 42]. In PPA, including SD (or sv-PPA), two small-cohort studies have suggested encouraging results with both TMS and tDCS [43, 44]. However, the authors did not target language-specific brain regions and the small number of patients precluded a counterbalanced study design. In addition, left-excitatory versus right-inhibitory TMS or tDCS have not been systematically evaluated to reveal the most efficient strategy in aphasia of neurodegenerative origin.

The purpose of this article is to present a clinical protocol (PHRC “STIM-SD”*)* implementing a multi-day tDCS regime in a large population of patients with SD (*n* = 60) specifically targeting the left ATL (with anodal stimulation) or the right ATL (with cathodal stimulation) to provide evidence for potential therapeutic effects and brain plasticity outlasting the duration of the treatment. This intervention builds on a previous pre-therapeutic double-blind, sham-controlled study by our team using a single tDCS session applied to the left and right ATL in patients with SD [45]. This approach allowed the comparison of left anodal (excitatory) to right cathodal (inhibitory) tDCS stimulation and showed that a single session of both left anodal and right cathodal tDCS resulted in transient but highly significant intra-semantic effects [45]. The goals of the present study include the evaluation of the potential therapeutic efficacy of periodical sessions of tDCS over the ATL during 10 days in language/semantic performance in patients with SD, the assessment of the time course of potential improvements, the exploration of potential effects on brain plasticity using functional connectivity measures (resting-state functional magnetic resonance imaging (fMRI)) and cortical metabolism (fluorodeoxyglucose positron emission tomography (FDG-PET)), the identification of the most efficient stimulation modality (left-anodal versus right-cathodal) and the identification of biomarkers such as ATL atrophy levels, which could be individually indicative of an efficient tDCS impact.

## Methods

### Study design

The *STIM-SD* protocol is a double-blind, sham-controlled, randomized study testing the efficiency of periodical tDCS sessions for 10 days (Monday to Friday for 2 weeks) using language/semantic assessments, and PET and MRI-based neuroimaging at four time points: baseline and 3 days, 2 weeks and 4 months after the end of the tDCS sessions (Fig. 1a, b, and Additional file 1). The patient population (*n* = 60) is randomly assigned to three subgroups each receiving a different treatment over the ATL: left-anodal tDCS (*n* = 20), right-cathodal tDCS (*n* = 20) and sham tDCS (*n* = 20).

**Fig. 1 Fig1:**
[figure not shown]
**a** Flow diagram from patients’ selection to the end of their participation in the study. tDCS, transcranial direct current stimulation; MRI, magnetic resonance imaging; PET, positron emission tomography; EEG, electroencephalography. **b** Standard protocol items: recommendations for Interventional Trials (Additional file 1). Table defining the different evaluations or interventions (left column) that would be performed for each study period or time point (top rows)

Language/semantic assessments are applied at the four time points by a set of computer-based tasks. For each task, we have developed two equivalent versions matched on various linguistic variables, which are used alternatively either at baseline or during follow-up evaluations, in a counterbalanced order across patient subgroups to avoid test/re-test confounds. Neuroimaging acquisitions (structural MRI, resting-state fMRI, FDG-PET) are performed at baseline and the 2-week time point. We also acquire resting-state electroencephalogram (EEG) recordings at baseline and after the end of tDCS sessions (3-day time point) given that patients with SD might have an altered pattern of resting state neuronal synchronizations [46].

To ensure double-blinding a first investigator (stimulator) performs and supervises the tDCS sessions, whereas a second investigator (evaluator) conducts the langue/semantic tasks, blinded to the stimulation condition (anodal, cathodal or sham). During sham stimulation, tDCS current is ramped up and down along 30 s respectively during the initial and final phases of the session, to emulate the transient skin-itching sensations characterizing active anodal or cathodal stimulation. Unnoticed by the patients, the stimulation unit is turned off during the 20-min sham tDCS session.

Stimulation sessions are applied daily for 10 days (Monday to Friday for 2 weeks). Each tDCS session lasts for 20 min. The direct current has an intensity of 1.59 mA (25cm^2^-round electrodes, current density of 0.06 mA/cm^2^). A group of 20 healthy subjects are also evaluated at baseline to provide normative values for language/semantic tasks and for imaging measures. Healthy participants do not undergo tDCS treatment and are only assessed once with the same language/semantic tasks and neuroimaging assessments performed by SD patients.

The primary endpoint of the *STIM-SD* protocol is to evaluate the potential therapeutic efficacy of multiday tDCS (10 days) on language/semantic performance in patients with SD (see the section “Language/semantic tasks” – the semantic association task). In addition, we will also (1) assess the time course of potential language/semantic improvement through the application of four follow-up time points; (2) assess neuroimaging biomarkers (PET and MRI) that could reflect stimulation-induced neuroplasticity and response to stimulation; (3) compare the effects of left-anodal and right-cathodal tDCS to define the most efficient stimulation modality; (4) identify biomarkers that could individually predict tDCS impact and (5) improve the understanding of the semantic roles of the left and right ATL and their potential structural connectivity, contributing to the definition of anatomic-functional models of semantics.

The protocol has been approved by the local Ethics Committee and is registered in ClinicalTrials.gov with the identifier NCT03481933 and the study title “‘Evaluation of a Transcranial Stimulation with Direct Current on Language Disorders in Semantic Dementia (STIM-SD)”*.* Written informed consent is obtained from all patients and healthy subjects before the onset of any of the study procedures. All research protocol visits take place at the same site, the Pitié-Salpêtrière Hospital. Two additional centers contribute to the protocol by recruiting patients with SD.

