### Randomization

A computer-generated block randomization list has been prepared by the Clinical Research Unit of the Pitié-Salpêtrière - Charles Foix Hospital group. The randomization list is integrated into the electronic case report form (eCRF) and a randomization number assigning patients to one of the three stimulation conditions (anodal, cathodal or sham tDCS) is attributed automatically upon completion of inclusion/non-inclusion criteria. The randomization is not stratified by center of inclusion because all stimulation sessions and time-point evaluations are performed at the Pitié Salpêtrière Hospital.

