### Language/semantic tasks

A set of computer-based language/semantic tasks is used to assess the potential effectiveness of tDCS. These tasks are carried out by patients at four time points: pre-tDCS (baseline) and 3 days, 2 weeks and 4 months after the end of the 10-day tDCS regime. The five language/semantic tasks are the following:
Semantic association task (SA)Picture naming task (NAME)Reading task (READ)Letter and category fluency task (FLU)Category judgment task (CJ)

Two additional tasks evaluating tDCS impacts on other cognitive functions are also applied:
Executive function task (EXE)Recognition of famous faces - a subtest of the French *Batterie Imagerie-Perception* (BIP).

The tasks are computer-programmed using E-Prime software (E-Prime®, Psychology Software Tools, Sharpsburg, PA, USA). Participants are comfortably seated in front of a laptop computer screen (HP EliteBook 8770w, USA) and a response box that records responses. Performance accuracy, reaction times and voice records are automatically registered by the software. The sessions are carried out in the presence of an investigator immediately after familiarization/training blocks comprising five trials for each task.

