#### Semantic association task (SA)

This task assesses semantic capacities and provides the primary endpoint criterion. It is based on the principle of the Pyramid Palm Trees Test [54]. The material includes 78 French words, which are grouped into 26 trials. Each trial includes three words, two of them are semantically related (the target item and test item), while the third word is a semantically unrelated distractor. The three words are displayed on the computer screen for 8 s and the participant has to decide, using two response buttons, if the target item (on top of the screen) is associated with the test item (on the bottom of the screen, either left or right) or the distractor item (on the bottom of the screen, either left or right, opposite to the test item). Thirteen test items appear on the left and 13 on the right. The lack of response during this 8-s time interval is recorded as an error. The task assesses two category dimensions using the contrast between trials containing only living items (*n* = 13) and trials containing only non-living items (*n* = 13). Two modalities of this task are applied: a verbal modality (described above) and a picture modality that uses pictures instead of words. The language stimuli (pictures or words) used in these two tasks for “living” and “non-living” trials are matched for (1) lexical frequency, (2) number of letters, (3) familiarity of words and pictures and (4) visual complexity of the pictures. Stimuli of version 1 and version 2 of the test are also matched for these four variables. Outcome measures will focus on performance (number of correct responses), and reaction times in milliseconds. Figure 3 illustrates different trials of the task.

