### Data analyses

We will accept a significance level of 5% (*p* < 0.05) corrected for multiple comparisons when needed. To assess our primary endpoint criterion, i.e., performance changes on the SA task, outcomes at baseline and at the 2-week time point will be compared using two-way analysis of variance with “time” (baseline, 2 weeks post-stimulation) and “group” (anodal, cathodal, sham) as factors. Since two comparisons will be made (sham versus left-anodal and sham versus right-cathodal tDCS) Dunnett’s two-tailed *t* test will be used to handle multiple comparisons. In the case that the data do not meet the normal distribution assumption, the non-parametric Mann-Whitney test will be used to compare performance improvements between the sham versus left-anodal and between the sham versus right-cathodal groups.

To assess the time course of potential improvements and test if such differ between the treatment groups, linear mixed models will be used with “time” (the four time points), “group” (anodal, cathodal and sham) and group-by-time interactions as fixed effects. The Benjamini and Hochberg method will be used for controlling for false discovery rate.

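### The stated primary ANOVA leaves out task-version order, a factor the design counterbalances; if baseline and 2 weeks use different versions, this costs power but is not shown to bias the contrast with sham

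*Protocol article*

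**What the plan says.** Under Methods, Study design (text following Fig. 1), the protocol article states: "For each task, we have developed two equivalent versions matched on various linguistic variables". These versions are ones "which are used alternatively either at baseline or during follow-up evaluations, in a counterbalanced order across patient subgroups to avoid test/re-test confounds". For the semantic association (SA) task, which supplies the primary endpoint, it adds: "Stimuli of version 1 and version 2 of the test are also matched for these four variables". On the size of that task it says: "The material includes 78 French words, which are grouped into 26 trials".

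The Language/semantic tasks section sets the assessments at "pre-tDCS (baseline) and 3 days, 2 weeks and 4 months after the end of the 10-day tDCS regime". The primary comparison is baseline against 2 weeks, so the primary visit is the third administration.

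The Data analyses section gives the primary model as a "two-way analysis of variance with “time” (baseline, 2 weeks post-stimulation) and “group” (anodal, cathodal, sham) as factors", followed by a two-tailed Dunnett test of each active arm against sham. The time-course model has time, group and their interaction. Neither model names version or version order.

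The Randomization section says that "a randomization number assigning patients to one of the three stimulation conditions (anodal, cathodal or sham tDCS) is attributed automatically". It does not mention version order either way.

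**The concern.** Two versions spread over four visits must repeat. If the repeat falls at or before the primary visit, counterbalancing can spread retest effects evenly but cannot remove them, so the stated aim of avoiding them is too strong.

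The statistical consequence lies in the model. Counterbalancing makes order a designed source of variation. If the baseline and 2-week versions differ, each patient's change contains the difficulty gap between versions, with one sign in one order and the opposite sign in the other. A model without order leaves that known variation in the residual. The trial has 20 patients per arm and, after Dunnett adjustment, power per comparison already below the stated 80%, so avoidable residual variance matters.

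**Working it through.** **1. The plan's own figure.** Inputs from the Sample size section: difference 15 points, SD 16 points, 20 per group, power 80%. The normal-approximation formula at two-sided 5% gives n = 2 × (1.960 + 0.842)² × (16/15)² = 17.9, so 18 per group (19 by exact t). A Bonferroni level of 2.5% gives 22. The stated 20 lies between these. Under the stated Dunnett test (critical value 2.27, 57 df), power at 20 per group is about 76% per comparison and 88% for at least one of the two. The 76% is the reference below.

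**2. Which items are seen at 2 weeks.** Call the versions A and B, and the visits baseline, 3 days, 2 weeks and 4 months.

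- One version at baseline and the other at follow-up (A-B-B-B): the 2-week items were seen at 3 days.
- Strict alternation (A-B-A-B): the 2-week items were seen at baseline.
- Of the eight sequences starting with A, only A-A-B-A and A-A-B-B leave the 2-week items unseen. Neither fits either reading of the text.

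**3. How a version difference enters the change score.** Let v be the mean score on A minus that on B, in points.

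- A-B-A-B: baseline and 2 weeks use the same version, so v cancels from the change.
- A-B-B-B and its mirror: the change contains −v in one order and +v in the other. With the orders 1:1, the variance of change is 16² + v².

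**4. Size on the second pattern.** One of 26 items is 100/26 = 3.8 points. The article gives no version difference, so 1 and 2 items are assumptions, and the SD of 16 is taken as free of version effects. The standardized contrast is 15 / (SD × √(2/20)), and power is approximately Φ(contrast − 2.27).

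| v | Variance of change | Ratio | SD | Contrast | Power per comparison |
|---|---|---|---|---|---|
| 0 | 256 | 1.00 | 16.0 | 2.96 | 76% |
| 1 item (3.8 points) | 256 + 14.8 | 1.06 | 16.5 | 2.88 | 73% |
| 2 items (7.7 points) | 256 + 59.2 | 1.23 | 17.8 | 2.67 | 66% |

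**5. Check by simulation.** This used three arms of 20, order exactly 10/10 in each arm, and version left out of the model. For v = 2, 4, 6 and 8 points, power per comparison was 74.9%, 73.0%, 70.3% and 65.8%. Familywise error was 4.7%, 4.1%, 3.3% and 2.6%, against 5.0% at v = 0. The arm means carry no bias. The test is conservative because the residual contains variation that balance has already removed from the arm difference. When order is added as a term (56 residual df), simulated power returns to about 76% for both 1 and 2 items.

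**6. Practice.** If every arm gains p points from seeing the items again, sham changes by p and active by p + 15. The contrast is still 15.

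**The case against.** The strongest reply is that the primary test is a randomized comparison with sham on the same tasks and visits. That stands. A practice gain shared by all arms cancels, and the article's success criterion is superiority to sham, not raw gain. A reader might infer that the primary result is confounded by retest effects. The documents do not support that, because it would need a practice gain that differs by arm, and nothing in the article establishes one.

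A reader might also take the Randomization section's silence to mean that version order is outside the list, or even that order follows arm, since the article speaks of balance across patient subgroups. Neither inference holds. That section describes only how arm is assigned. The Study design section does state counterbalancing, and balancing within each arm is its ordinary meaning. Blinding of the evaluator is no obstacle, because a version code need not reveal the arm. Even if order were left to chance, familywise error would stay at about 5%, and imbalance would add only 0.6 to 2.5 points (SD) to an arm difference for v of 2 to 8.

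Three further points limit the size. The SA versions are matched on four variables, so v may be near zero. The SD of 16 comes from the earlier study and may already include version effects, in which case the loss is partly counted twice. Under strict alternation the term recovers nothing.

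Finally, covariates are often left to an analysis plan. Here, however, the article does state the factors of the primary model, and a factor the design counterbalances is not among them.

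**Conclusion.** The point holds as one of precision and wording. On either natural reading the 2-week visit reuses items, so retest effects are limited, not avoided. The primary contrast is not shown to be biased.

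Leaving version order out of the stated ANOVA costs power only if baseline and 2 weeks use different versions. The cost is about 3 points of power per comparison for an assumed 1-item difference and about 10 points for 2 items, with a conservative test when order is balanced within arm. These figures rest on an assumed v, on an SD of 16 free of version effects, and on scoring over 26 trials.

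It may be tempting to reorder the versions so that the 2-week items are new. That would only move the repetition to other analysed visits, and it would change the measurement sequence after 13 patients had been randomized (Trial status). It is a trade-off and does not follow from this point.

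**What to change.** 1. Add version order (by time) as a factor in the primary and time-course models. In an analysis of change from baseline to 2 weeks this is a single order term.
2. Balance order 1:1 within each arm (10/10), using a version code pre-assigned by patient number. The evaluator then learns the version but not the arm.
3. In the Study design text, replace *avoid* with *limit* for the effect of the two versions on retest confounds.

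The cost is one residual degree of freedom in the primary comparison (57 to 56), which does not visibly change power when v is zero. With four visits, the order-by-time interaction in the time-course model takes three. No new material, visits or patients are needed.
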